#### Exclusion.

Large territorial infarction or marked cerebral atrophy on MRI.Bilateral ICA occlusion or concomitant neurovascular disease (e.g., cerebral aneurysm or arteriovenous malformation).Severe systemic comorbidities, life expectancy <2 years, or a mRS score >3.Cardiac conditions that are associated with a high risk of cerebral embolism (e.g., prosthetic heart valves, infective endocarditis, intracardiac thrombus, sick sinus syndrome, cardiac myxoma, or cardiomyopathy with left ventricular ejection fraction <25%; atrial fibrillation, patent foramen ovale, and atrial septal aneurysm are not exclusion criteria).Contraindications to MRI, CTA, DSA, iodinated contrast agents, or required perioperative antiplatelet therapy.Non-functioning STA-MCA bypass.Participation in another interventional or experimental study within the previous 12 months, including those involving ionizing radiation.Pregnancy.

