### Study population, settings and eligibility criteria

#### Study Population.

Patients with chronic ICA occlusion who underwent elective STA-MCA bypass surgery were enrolled between July 2025 and December 2027.

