#### Surgical treatment.

Eligible patients with chronic ICA occlusion will undergo standard STA-MCA bypass surgery. The procedure will be carried out using a standardized microsurgical end-to-side anastomosis technique. Intraoperative selection of the donor STA branch and recipient MCA segment will be based on vessel diameter, flow characteristics, and surgical accessibility. Intraoperative bypass patency will be assessed using the “faucet” technique” [22] in combination with microscopic indocyanine green (ICG) angiography to ensure adequate flow through the anastomosis.

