#### Postoperative study procedures.

Within 1-3 days after surgery, CTA of the head and neck will be performed to confirm bypass patency, measure the caliber of the donor STA branch, and visualize its course. At 3–5 days postoperatively, ASL-based MR perfusion imaging will be conducted to evaluate cerebral perfusion changes compared with preoperative studies. 3D segmentation and quantitative perfusion mapping will be applied to provide an objective assessment of regional perfusion improvements following surgery. Before hospital discharge, all patients will undergo a repeat evaluation of neurological status and cognitive function using the same standardised tests as preoperatively.

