#### Definitions of outcomes.

The primary outcome is defined as the incidence of ischemic stroke during the 6-month follow-up period after surgery. This outcome will be assessed based on clinical evaluation and confirmed by neuroimaging (MRI or CT) in cases of suspected new neurological deficits, in accordance with standard diagnostic criteria for ischemic stroke.

Secondary outcomes included early postoperative haemodynamic change (≤7 days) assessed using the same imaging modality; graft patency was defined as uninterrupted flow through the bypass on intraoperative ICG and postoperative CTA; changes in cerebral haemodynamic status from baseline to 6 months after surgery will be assessed using ASL MRI and defined as a quantitative increase in regional CBF in the affected hemisphere and/or a reduction in interhemispheric perfusion asymmetry compared with baseline; change in neurological status from baseline to 6 months assessed using the NIHSS and the mRS; changes in cognitive function from baseline to 6 months based on standardised neuropsychological testing; all-cause mortality at 6 months; perioperative complications within 30 days (including intracranial haemorrhage, hyperperfusion syndrome, seizures, wound complications, and graft occlusion); and angiographic extent of revascularisation on follow-up imaging.

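### The exclusion for a non-functioning STA-MCA bypass is not limited to earlier surgery; read as the study graft, it conditions inclusion on an outcome the study reports

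*Protocol article*

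**What the plan says.** The Exclusion list of the protocol article includes "Non-functioning STA-MCA bypass". The entry stands alone, with no time point and no qualifier such as 'previous'.

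Four other places bear on its meaning:

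- **Study Population:** "Patients with chronic ICA occlusion who underwent elective STA-MCA bypass surgery were enrolled between July 2025 and December 2027".
- **Surgical treatment:** "Eligible patients with chronic ICA occlusion will undergo standard STA-MCA bypass surgery". Flow is checked during the operation by the faucet technique "in combination with microscopic indocyanine green (ICG) angiography to ensure adequate flow through the anastomosis".
- **Postoperative study procedures:** "Within 1-3 days after surgery, CTA of the head and neck will be performed to confirm bypass patency".
- **Definitions of outcomes:** as a secondary outcome, "graft patency was defined as uninterrupted flow through the bypass on intraoperative ICG and postoperative CTA". Another secondary outcome is "perioperative complications within 30 days (including intracranial haemorrhage, hyperperfusion syndrome, seizures, wound complications, and graft occlusion").

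The Statistical analysis section reports patency, recurrent events, complications and deaths as percentages with 95% intervals. Nothing in the article says whether a patient whose study graft fails stays in those denominators.

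**The concern.** An exclusion criterion should be decidable before treatment. Whether the study bypass functions is a result of treatment, and the protocol itself measures it as an outcome. If the criterion is applied to the study graft, the patients it removes are the ones the patency and graft-occlusion outcomes exist to count. The study would then describe patients after a technically successful bypass, whereas the Discussion sets out to characterise events and recovery after STA-MCA bypass in the selected cohort. The primary outcome, ischaemic stroke over 6 months, would be estimated in the same filtered group.

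**Working it through.** **1. What the criterion can refer to**

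| Source | Points to the study graft | Points to an earlier bypass |
|---|---|---|
| Exclusion list | No 'previous', no date | The neighbouring criteria can be judged before surgery |
| Study Population | Patients who had the operation were enrolled | The article also uses the past tense for planned work, so this is weak evidence |
| Surgical treatment | The named bypass is the study operation; flow is first checked during it | Patients are already called eligible before they are operated on |
| Table 1 | Bypass patency is scheduled at PostOp0, PostOp6 and UV, not Preop; no medical-history row lists a previous bypass | No post-surgery eligibility check is described |
| Definitions of outcomes | – | Patency and graft occlusion make sense as outcomes only if failures stay in |

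The study-graft reading is the more natural one, because the only STA-MCA bypass the article describes is the study operation and no preoperative check of a bypass is scheduled. It is not proven.

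**2. The plan's own figure**

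The article gives no figure for this point. The nearest is the sample size: paired t-test, two-sided 0.05, standardised effect 0.40, correlation 0.5. With dz = 0.40/√(2(1 − 0.5)) = 0.40, the noncentral t gives n = 52 for 80% power and 86.2% power at 60, as stated. The point does not depend on it. Only the 0.40 is reused in step 4.

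**3. Early patency if the rule is applied to the study graft**

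Take 60 operated patients, k of them with early failures. The values of k are assumed. All operated: (60 − k)/60. After exclusion: (60 − k)/(60 − k) = 100%. Intervals are exact.

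| k | All operated (95% CI) | After exclusion (lower limit) |
|---|---|---|
| 3 | 57/60 = 95.0% (86.1–99.0) | 57/57 = 100% (93.7) |
| 6 | 54/60 = 90.0% (79.5–96.2) | 54/54 = 100% (93.4) |
| 9 | 51/60 = 85.0% (73.4–92.9) | 51/51 = 100% (93.0) |

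The 100% follows from the rule and needs no assumption about risk. It does assume that every early failure is excluded.

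**4. Perfusion (illustration)**

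Assume failed grafts gain nothing, a standardised change of 0.40 is seen in functioning grafts, and the standard deviation is unchanged. With failure fraction f, the change in all operated patients is (1 − f) × 0.40:

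- f = 2%: 0.392
- f = 5%: 0.38
- f = 10%: 0.36
- f = 15%: 0.34

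The overstatement is 1/(1 − f) − 1, or about 2% to 18%.

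**5. Stroke (illustration)**

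Incidence in all operated patients = (1 − f) × 5% + f × r, where 5% is an assumed risk with a functioning graft and r an assumed risk without one. After exclusion it is 5.0%.

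| f | r = 5% | r = 15% | r = 30% | r = 50% |
|---|---|---|---|---|
| 5% (3/60) | 5.0% | 5.5% | 6.25% | 7.25% |
| 10% (6/60) | 5.0% | 6.0% | 7.5% | 9.5% |
| 15% (9/60) | 5.0% | 6.5% | 8.75% | 11.75% |

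The first column shows that there is no distortion if graft failure does not change stroke risk.

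**The case against.** The best defence is that the phrase means a failed bypass already present at screening. The rest of the list can be judged before surgery, the surgical section treats eligibility as settled before the operation, and the patency and occlusion outcomes would be coherent. This stands as a possible intention, and it means a reader should not infer that the protocol certainly discards failed study operations. It does not remove the point: nothing in the wording confines the criterion to earlier surgery, so it can be applied to the study graft.

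Three further limits stand:

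- **Later occlusions.** If the rule acts only on failure seen in theatre or on the first CTA, occlusions up to 30 days or 6 months would still be counted. Those figures would be less affected than early patency.
- **Stroke.** It is tempting to say that failed grafts carry the most strokes and to quote a size. The documents give neither a failure rate nor a risk by graft status, and the Introduction cites a trial that found no fewer strokes despite better haemodynamics. With 60 patients, 3 strokes (5%) has an exact interval of about 1.0% to 13.9%, which covers every value in the stroke table.
- **Comparison with medical treatment.** A reader might infer a bias in favour of surgery. There is no control arm and the Discussion disclaims comparative efficacy, so the most that can be said is that results would look better than in all operated patients.

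**Conclusion.** The point holds as an undated criterion whose most natural reading selects on a post-treatment outcome and contradicts the protocol's own patency and graft-occlusion outcomes. Being a conflict between stated passages, it goes beyond detail that an article may leave to a fuller document.

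On the study-graft reading, the direction is certain for early patency, which moves towards 100% whatever the true rate. For perfusion it depends on failed grafts gaining less, and for stroke on failed grafts carrying a higher risk. The sizes shown for both rest wholly on assumed inputs. Whether the criterion is in fact being applied this way cannot be settled from the article.

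**What to change.** Reconcile the Exclusion list with Study Population, Surgical treatment and Definitions of outcomes:

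1. State that no patient is excluded or removed because the study bypass is not functioning.
2. Define the analysis set as every consented patient in whom the study operation was started. Use it for stroke, death, complications, patency, perfusion and the neurological and cognitive scores.
3. Count a non-functioning study graft as a patency failure.
4. Label any analysis restricted to functioning grafts as secondary, and give the number of patients left out.
5. If the criterion was meant for a bypass that had already failed at screening, say so, for example: 'pre-existing STA-MCA bypass from earlier surgery that is not functioning'. Wording that covers any earlier bypass would go further, because it would also exclude patients whose earlier bypass still works.

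The cost is a one-line amendment and a sentence on the analysis set. Enrolment is stated to run to December 2027, so further exclusions can be prevented; any patient already removed on this ground should be identified and reported. The downside is that patency and event figures may be less favourable.

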## Study procedure and intervention

### Clinical and radiological assessments

#### Radiological assessment.

The assessment schedule is given in Table 1. To evaluate the ICA occlusion, a three-level assessment will be conducted using CTA of the head and neck vessels, MRI ASL and Time-of-flight (TOF) sequences, and a confirmatory assessment of occlusion during DSA. All imaging studies will be performed and interpreted by neuroradiologists and neurosurgeons, with findings reviewed collaboratively.

**Table 1 pone.0354103.t001:** Data collection schedule.

Assessments	Preop	PostOp0	PostOp6	UV

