#### Patient selection.

The study requires a multidisciplinary team comprising a neurologist, neurosurgeon, neuropsychologist, neuroradiologist, biostatistician, and research administrator.

Patients will be identified through the Department of Vascular and Functional Neurosurgery. STA-MCA bypass procedures for patients with chronic ICA occlusion will be performed by a team of neurosurgeons within the department. Neurosurgeons must have experience in vascular anastomosis and have successfully conducted STA-MCA bypass surgery on at least 10 patients. Neurological and cognitive assessments will be conducted by a consultant neurologist and neuropsychologist. All radiological imaging will be independently reviewed and interpreted by two radiologists from the Department of Radiology.

Baseline symptomatic status will be incorporated as an adjustment variable in multivariable and longitudinal analyses to account for differences in baseline risk and recovery potential. Exploratory subgroup analyses by symptom status will be performed where sample size permits.

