#### Intraoperative perfusion and blood flow direction assessment.

Intraoperative perfusion and blood flow direction will be assessed using ICG fluorescent angiography with the Carl Zeiss Pentero 800 microscope equipped with FLOW 800 technology, which allows real-time visualization of cerebral vessels. All data will be processed and analyzed to create a color map depicting hemodynamic and perfusion delays. This enables comparison of perfusion parameters in the anastomosis region before and after bypass surgery, as well as assessment of blood flow direction and hyperperfusion zones in the brain. The assessment will be performed by neurosurgeons.

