### Statistical analysis

Continuous variables will be reported as mean with standard deviation or median with interquartile range, depending on distribution. Categorical variables will be presented as frequencies and percentages. The primary outcome, change in cerebral hemodynamic status from baseline to 6 months, will be analyzed using a paired t-test or Wilcoxon signed-rank test, depending on data distribution. Mean change in CBF and/or perfusion asymmetry will be reported with 95% confidence intervals.

Early postoperative and 6-month changes in neurological and cognitive scores will be analyzed using paired tests. Categorical outcomes, including graft patency, recurrent TIA or stroke, complications, and mortality, will be reported as proportions with 95% confidence intervals.

Where appropriate, exploratory regression analyses will be performed to identify factors associated with hemodynamic improvement and clinical outcomes. Potential predictors may include age, sex, baseline perfusion deficit, vascular risk factors, duration of symptoms, and preoperative neurological status. Given the limited sample size, multivariable models will be restricted to a small number of clinically relevant covariates.

Because repeated measurements will be obtained from the same participants, analyses will account for within-subject correlation. Continuous repeated outcomes will be analysed using linear mixed-effects models, with time point entered as a fixed effect and participant ID as a random intercept. This approach allows estimation of postoperative change while accounting for correlation between repeated measures within individuals and accommodating incomplete follow-up data under a missing-at-random assumption.

A p-value <0.05 will be considered statistically significant. All analysis will be performed using Stata 19.5.

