### Limitations

This study has several limitations. First, its single-center, open-label design may limit the generalizability of the findings and introduces a potential risk of selection bias. However, conducting the study in a high-volume tertiary neurosurgical center ensures consistency in surgical technique, perioperative management, and imaging protocols.

Second, the absence of a non-surgical control group precludes direct comparison between surgical revascularisation and best medical therapy. Nevertheless, the primary objective of this study is not to reassess the efficacy of STA-MCA bypass versus conservative treatment, but rather to investigate detailed hemodynamic, neurological, and cognitive changes following bypass surgery in a carefully selected population with documented cerebral hypoperfusion.

Third, the planned sample size of 60 participants was primarily determined based on feasibility considerations, including the recruitment capacity of our center, the predefined study duration, and the scope of the funded grant project. As a result, the planned sample size may limit statistical power for detecting small effect sizes and for building robust predictive models. Therefore, multivariable analyses will be considered exploratory, and results will be interpreted cautiously. Larger multicenter studies will be required to externally validate the findings.

Fourth, the single-arm study design without a control group limits the ability to control for confounding factors and precludes definitive causal inference regarding the observed effects. As a result, the findings should be interpreted as associative, and residual confounding cannot be excluded despite adjustment in exploratory analyses.

Fifth, cognitive assessment may be influenced by learning effects, mood, fatigue, or educational background. To mitigate these factors, standardized testing conditions will be applied, parallel test versions will be used when available, and cognitive reserve indicators will be incorporated into the analysis.

Sixth, advanced imaging techniques such as ASL MRI and intraoperative ICG FLOW800 analysis require specialized equipment and expertise, which may limit reproducibility in lower-resource settings. However, these techniques provide unique insights into cerebral hemodynamics and represent a major strength of the study.

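### The protocol gives two accounts of who reads the images and does not say which supplies the study data; one of them lets the operating team take part

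*Protocol article*

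**What the plan says.** Two sections of the protocol article describe how images are read.

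- Patient selection: "All radiological imaging will be independently reviewed and interpreted by two radiologists from the Department of Radiology".
- Radiological assessment: "All imaging studies will be performed and interpreted by neuroradiologists and neurosurgeons, with findings reviewed collaboratively".

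Patient selection also says who operates: the bypasses "will be performed by a team of neurosurgeons within the department". For intraoperative ICG angiography, the section on intraoperative perfusion and blood flow direction says: "The assessment will be performed by neurosurgeons".

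Definitions of outcomes then takes several secondary outcomes from these images. For patency, "graft patency was defined as uninterrupted flow through the bypass on intraoperative ICG and postoperative CTA". Haemodynamic change on ASL MRI is "defined as a quantitative increase in regional CBF in the affected hemisphere and/or a reduction in interhemispheric perfusion asymmetry compared with baseline". The angiographic extent of revascularisation at follow-up is also listed. Ischaemic stroke, the primary outcome in that section, rests on clinical evaluation with MRI or CT confirmation when a new deficit is suspected.

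**The concern.** Both statements claim to cover all imaging, but they name different readers and different procedures. The first gives two independent radiologist readings. The second gives an interpretation shared between radiology and neurosurgery. Neither is designated as the reading that enters the database, and the article gives no order between them.

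This matters because of the design. There is no control arm and treatment is open, so every imaging outcome is a judgement about how an operation turned out, made by people who know it took place. If the shared reading supplies the data, members of the department that performed the bypass help decide whether its graft is patent and how far the territory is revascularised. The study also aims to relate perfusion change to neurological and cognitive recovery. A reader who knows the clinical course could let it colour the reading, which would put that relation at risk as well.

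**Working it through.** No figure in the plan depends on this point and no formula applies. The check compares the text of the sections.

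**1. Do the two statements cover the same images?** The Radiological assessment sentence follows a description of confirming the carotid occlusion, so a preoperative scope is conceivable. But it says all imaging studies, and its section opens by pointing to the schedule in Table 1. That schedule has CTA and ASL MRI preoperatively, immediately after surgery and at 6 months. As written, both statements reach the postoperative images.

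**2. Can they be reconciled?** Yes, in one way: the radiologists read independently of each other and the findings then go to a joint review. The article does not state this sequence. Even under it, neurosurgeons interpret the images, and nothing says whether the recorded result is the one before or after the joint review.

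**3. Could the operating team be among the readers?** Surgeons of the department operate, and neurosurgeons are named as interpreters. No sentence excludes the surgeon who operated on a given patient, and none says that this surgeon reads. The supported statement is that the operating team could take part.

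**4. Which measurements are exposed?**

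| Measurement | Source after surgery | Room for reader judgement |
|---|---|---|
| Graft patency | Intraoperative ICG and postoperative CTA | ICG is already assessed by neurosurgeons; CTA is the only part that can be read independently of them |
| Extent of revascularisation | Follow-up angiographic imaging; CTA in Table 1, where DSA is preoperative only | Substantial |
| Infarct burden | Scheduled in Table 1 at all three main time points; not in the outcome definitions | Some |
| CBF and asymmetry | ASL MRI | Less: quantitative values, 3D segmentation and perfusion mapping |
| Ischaemic stroke | Clinical evaluation, confirmed by MRI or CT | Only through the confirmation |

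**5. Could it reach the primary analysis?** Statistical analysis says: "The primary outcome, change in cerebral hemodynamic status from baseline to 6 months, will be analyzed using a paired t-test". This conflicts with Study endpoints and Definitions of outcomes, where stroke is primary. If the analysis section states the intended primary outcome, the unclear reading process applies to it directly, though in its most quantified form.

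**6. Is the risk acknowledged?** Limitations says of the study that "its single-center, open-label design may limit the generalizability of the findings and introduces a potential risk of selection bias". Bias in assessing outcomes is not mentioned there.

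**The case against.** The strongest reply is that this is an unclear sequence and not a contradiction. Independent readings followed by a joint discussion would satisfy most of both sentences. That stands: a reader might infer that the two statements cannot both be true, and the text does not prove it. What remains is that the article does not say which result is recorded.

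Second, much of the imaging is measured. CBF is quantitative, perfusion mapping uses segmentation, donor artery calibre has a stated measuring site, and patency has a definition. This also stands and lowers the risk for perfusion and calibre. It does less for patency and extent of revascularisation.

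Third, a reader might infer that the results will be biased in favour of surgery and that the correlation between perfusion and cognition will be inflated. The documents do not support either as fact. A psychologist gives the cognitive tests, a neurologist does the neurological examination, and Neurological assessment says results are collected and recorded separately before they enter the database. Nothing says image readers see the scores.

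Fourth, a reader might infer that the stroke endpoint is compromised. It is clinically evaluated, and imaging only confirms suspected events.

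Fifth, masking of readers, adjudication and agreement statistics are details that an article commonly leaves to the full protocol. Their absence is not the point here. The point is that the article makes two differing statements about who reads and designates neither.

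**Conclusion.** The point holds as an unresolved conflict over which reading is the study reading, with an avoidable risk of bias attached. Under the Radiological assessment wording, neurosurgeons, possibly including those who operated, could influence postoperative CTA patency, extent of revascularisation and infarct burden, and to a lesser degree ASL perfusion change. Stroke is reached only through imaging confirmation.

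The size of any bias cannot be computed. The document gives no rate of equivocal readings, no expected patency and no reader agreement, so any number would be invented.

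The conclusion rests on two readings of the text: that all imaging studies includes the postoperative ones, and that silence about the operating team leaves it eligible to read. If a fuller document already makes the radiologists' independent reading the source of study data, only the article's wording needs correcting. The change is worth making because the safeguard is already planned and costs almost nothing to secure.

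**What to change.** Amend Radiological assessment so that CTA and MRI study endpoints use the reading described under Patient selection, and state that:

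- the two radiologists are not part of the operating team;
- each records results before any joint review and without access to clinical or cognitive scores;
- disagreements are resolved between the two of them;
- the collaborative review with neurosurgeons serves clinical care and does not change the recorded study result.

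This does not cover intraoperative ICG, which neurosurgeons assess and which is part of the patency definition. Report CTA patency from the independent reading separately from the intraoperative ICG result, so that readers can see the component not judged by the surgical team.

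The cost is a few sentences and a small change in reading order. Both radiologists are already planned, so no staff are added, and treatment is unaffected.
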